## Abstract

**Background:** Research conducted in Western countries has suggested that high-dose statin therapy can lead to the regression of carotid atherosclerotic plaques and can reduce periprocedural ischemic complication rates in individuals undergoing carotid artery stenting (CAS). However, whether this same therapeutic approach is of value in patients of Chinese ethnicity is not as well-established.

**Methods:** This is a single-center, prospective, parallel-controlled, intervention-based efficacy study that will enroll a total of 130 Chinese patients with cervical carotid stenosis who are scheduled to undergo CAS. These patients will be randomly divided into a routine treatment group and a high-dose atorvastatin group. Individuals in the routine treatment group will be administered standard of care 20 mg/day atorvastatin treatment. Individuals in the high-dose atorvastatin group will be administered 80 mg/day atorvastatin for 3 days prior to and following CAS. The primary outcome of this study will be the cumulative incidence of new cerebral ischemic lesions on diffusion-weighted magnetic resonance imaging (DW-MRI) within 5 days following CAS, and of transient ischemic attacks (TIAs) or ischemic stroke within 30 days after CAS.

**Discussion:** This study is the first to assess whether high-dose atorvastatin treatment is capable of reducing the incidence of perioperative cerebral ischemic injury in patients of Chinese ethnicity undergoing CAS. These results will offer evidence regarding which statin treatment regimens are more appropriate when treating Chinese patients undergoing CAS in an effort to minimize their risk of any perioperative cerebral ischemic injury.

**Trial Registration:**
ClinicalTrials.gov NCT03079115; registered March 14, 2017.

## Introduction

### Perioperative Ischemic Stroke of CAS

Carotid artery stenting (CAS) is frequently employed to treat patients suffering from stenosis of the carotid artery, but this procedure is associated with a relatively pronounced perioperative risk of ischemic complications, of which up to 90% occur within 7 days following treatment (1, 2). One recent meta-analysis determined that ~40.3% of CAS patients suffer from the development of new cerebral ischemic lesions that are visible upon diffusion-weighted magnetic resonance imaging (DW-MRI) following surgery (3). These patients that exhibit new ischemic foci are in turn more likely to suffer from a subsequent stroke or transient ischemic attacks (TIA) during follow-up (4), and they are more likely to exhibit cognitive decline (5).

### High-Dose Statin Therapy as a Means of Achieving Neuroprotection in CAS Patients

Current guidelines for patients undergoing CAS indicate that patients should receive statins during the perioperative period, but the dosage or duration of such statin administration is not specified (6). The high-dose administration of atorvastatin (80 mg/day) has been found to mediate a number of potentially neuroprotective effects, including enhanced protection of vascular endothelium, blood vessel dilation, and reduced rates of thrombosis. In a study of carotid stenosis patients from Western nations, such high-dose atorvastatin administration was shown to result in a lower risk of the development of new ischemic lesions following CAS surgery, and to be protective for cerebrovascular and brain tissues (7).

As there are potentially significant differences between populations of different genetic backgrounds with respect to their responses to statin therapy, whether high-dose atorvastatin administration is associated with the same benefits in patients of Chinese ethnicity undergoing CAS is not as well-understood. As such, the present article outlines the design of a PICAS study aimed at evaluating the safety and efficacy of high-dose atorvastatin administration during the perioperative period in patients of Chinese ethnicity undergoing CAS. The primary aim of this study is to assess the ability of such high-dose atorvastatin treatment to reduce the incidence of ischemic brain injury in CAS patients of Chinese ethnicity. The secondary aim of this study is to determine whether there are any differences in the safety profiles of normal- and high-dose atorvastatin regimens.

## Methods and Analysis

### Study Design

This is a single-center, single-blind, prospective, parallel-controlled, intervention-based efficacy study that will enroll 130 consecutive patients suffering from carotid stenosis that are scheduled to undergo carotid artery stenting in Beijing hospital. The study process is summarized in Figure 1.

**Figure 1 F1:**
[figure not shown]
Study design. CAS, carotid artery stenting; MRI, magnetic resonance imaging; DW-MRI, diffusion-weighted magnetic resonance imaging.

### Randomization

All patients will be randomized into either a routine treatment group or a high-dose atorvastatin group. These patients will be subjected to a stratified blocked randomization method that will assign individuals to treatment groups based upon age(> 70 years or not) and presentation (symptomatic or asymptomatic). Random number generation by a dedicated software program will then be used to assign patients to groups with 1:1 matching grouping and no cross-grouping are permitted.

### Intervention

Individuals in the high-dose group will be administered 80 mg/day atorvastatin beginning 3 days prior to CAS and continuing until 3 days following CAS, whereas routine treatment group patients will receive 20 mg/day atorvastatin during this same period. For the remainder of hospitalization and after discharge, all patients will be administered 20 mg/day atorvastatin. Cerebral protection devices will be required for all patients, but the form of the protective device, the type of stent used, and the interventional strategy will be left to clinical discretion.

Before the CAS procedure, six-vessel DSA is routinely performed. Symptomatic patients with carotid stenosis <50% and asymptomatic patients with carotid stenosis <70% confirmed by cerebral angiography will be excluded from this study.

During the CAS procedure, the distal embolic protection device will be used for all patients. Type of distal protective device (Spider FX., Medtronic; Emboshield NAV, Abbott), carotid stent (Precise, Cordis; Protégé, Medtronic; Acculink, Abbott), pre- and post- dilatation balloon (Ryujin plus, Terumo; Sterling, Boston Scientific, Viatrac, Abbott) will be left to operators' discretion.

Within 5 days prior to CAS, all patients will undergo an MRI examination (including DW-MRI), a neurological assessment, and blood sampling in order to test for parameters such as hematological findings, lipid levels, and hepatic/renal function. In addition, all patients will receive routine standard of care treatment including aspirin (100 mg/day prior to CAS for ≥ 3 days, or a 300 mg loading dose at 6 h prior to CAS) and clopidogrel (75 mg/ day prior to CAS for ≥ 3 days, or a 300 mg loading dose at 6 h prior to CAS). All patients will receive platelet aggregation tests using optical aggregometry before the procedure, and those who show clopidogrel resistance will switching to ticagrelor 90 mg, twice a day. Patients will then undergo routine conventional dual antiplatelet aggregation treatment for 3 months, followed by long-term aspirin administration (100 mg/day). Within 5 days following the CAS operation, all study subjects will again be subjected to DW-MRI and blood tests of the same parameters measured preoperatively.

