### Outcomes

The primary outcome for this study will be the cumulative incidence of new ischemic lesions on post-CAS cerebral DW-MRI, TIA or ischemic stroke within 30 days after CAS. For this analysis, stroke is defined as any neurological deficits that persist for over 24 h by a vascular cause, including cerebral infarction, intracerebral hemorrhage (ICH), and subarachnoid hemorrhage (SAH). TIA is defined as any neurological deficit (cerebral or ocular) that is newly evident and consistent with focal cerebral ischemia but that resolved within a 24 h period (including localized muscular weakness, language dysfunction, transient monocular blindness, or the need for assistance while walking.

In addition, this study will have the following secondary outcomes: (1) the incidence of new ischemic lesions as detected via cerebral DW-MRI within the period of 5-day following CAS; (2) the number of new lesions and the incidence of new lesions >5 mm in size as detected via DW-MRI within this 5-day postoperative period; (3) the incidence of ischemic stroke or TIA within 30 days postoperative period; (4) the incidence of death, any stroke, or myocardial infarction within 30 days postoperative period; (5) rates of bleeding complications, as determined based upon the Thrombolysis In Myocardial Infarction criteria (8), and of entry-site complications (subcutaneous hematoma >10 cm, pseudoaneurysm or arteriovenous fistula).

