Studies of Western populations have observed a 17% incidence of new ischemic lesions in patients treated with 120 mg atorvastatin prior to CAS, as detected via DW-MRI (7). Additional research suggests that micro-emboli detachment can still occur 1 day post-CAS. As such, the use of atorvastatin for a longer duration both pre- and post-CAS may be associated with lower rates of new ischemic lesion formation. As previous studies have demonstrated that 3 days of continuous oral dosing with atorvastatin is sufficient to achieve steady-state plasma concentrations in patients with significant reductions in LDL levels in treated patients (12, 13), we plan to provide patients in this study with a loading dose regimen wherein they begin taking an oral loading dose of atorvastatin 3 days prior to CAS and continue to do so for 3 days postoperatively. The goal of this approach is to take into account both the safety of patients and the practicality of implementing such a dosing regimen.

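### The single post-CAS DW-MRI may be taken at any time from day 0 to day 5, so a compliant early scan can miss later silent lesions and the effect of post-CAS doses not yet given

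*Protocol article*

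**What the plan says.** **Scan timing.** The Intervention section schedules one post-procedural scan: "Within 5 days following the CAS operation, all study subjects will again be subjected to DW-MRI". The lesion definition under MRI Protocol compares post-intervention with pre-treatment imaging and adds no timing.

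**Dosing period.** The same section gives the high-dose arm "80 mg/day atorvastatin beginning 3 days prior to CAS and continuing until 3 days following CAS", with the routine dose over the same days in the other arm.

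**Rationale.** The Discussion argues: "Additional research suggests that micro-emboli detachment can still occur 1 day post-CAS". It continues that "the use of atorvastatin for a longer duration both pre- and post-CAS may be associated with lower rates of new ischemic lesion formation". Sample Size Estimates supports the 15% high-dose rate by therapy being longer than in the earlier statin trial.

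**Masking.** The registration table in the Appendix masks the outcomes assessor only. MRI Protocol has the images read by neuroradiologists blinded to patient history and procedure.

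**Outcome wording.** The Abstract counts DW-MRI lesions "within 5 days following CAS, and of transient ischemic attacks (TIAs) or ischemic stroke within 30 days after CAS". The primary outcome under Outcomes reads "new ischemic lesions on post-CAS cerebral DW-MRI, TIA or ischemic stroke within 30 days after CAS", and the Appendix table has almost the same words. Under Outcomes, the first two secondary outcomes put DW-MRI lesions in a 5-day period.

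**The concern.** A scan a few hours after the procedure and a scan on day 5 both comply with the plan, so time at risk for imaging lesions can differ by up to 5 days between patients. That range spans the whole post-CAS part of the randomised dosing. A patient scanned on day 0 or 1 contributes an imaging result that precedes most of the post-CAS doses and any silent lesion formed later. The measurement rule therefore allows part of the effect behind the 15% assumption to go unseen.

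Two consequences are possible. Early scans spread evenly over the arms lower both observed rates and reduce power. Early scans that are more common in one arm would bias the comparison. Blinded reading protects the interpretation of images, not the choice of scan day, and the staff who book the scan may know the allocation.

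**Working it through.** **1. The plan's own sample size.** Inputs from Sample Size Estimates: 40% v 15%, two-sided alpha 0.05, 1:1 allocation. Power is printed as 0.08 and is read here as 0.80, since 0.08 would give only 3 per group (9 with continuity correction).

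- Pooled formula: n = [1.960·√(2·0.275·0.725) + 0.842·√(0.40·0.60 + 0.15·0.85)]² / 0.25² = 48.9, so 49 per group.
- With continuity correction: (48.9/4)·[1 + √(1 + 4/(48.9·0.25))]² = 56.6, so 57 per group. The plan states 56, so it is reproduced to within rounding.
- Evaluable patients after the planned 15% dropout: 65 × 0.85 = 55.25, so 55 per arm.

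**2. Power with nothing missed.** Exact enumeration of two binomials with 55 per arm, two-sided 0.05: 40% v 15% gives 0.852 (uncorrected chi-squared) and 0.798 (Fisher).

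**3. What an early scan can and cannot capture.**

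| Source of effect or event | Seen with a day 0-1 scan? |
|---|---|
| Lesions from the procedure itself | Largely yes |
| Effect of the 3 days of pre-CAS dosing on those lesions | Yes |
| Late events with symptoms | Yes, through TIA or ischemic stroke to day 30 |
| Silent lesions formed after the scan | No |
| Effect of post-CAS doses not yet given on silent lesions | No |

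**4. Illustration of dilution, equal timing in both arms.** Let L be the share of lesion-positive patients who become positive only late, and s the share of scans done before that. Visible rate = true rate × (1 − s·L). The documents give neither L nor s, so both are assumptions. The whole primary endpoint is treated as imaging-driven, which overstates the loss somewhat.

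| L | s | Visible rates | Power, chi-squared / Fisher |
|---|---|---|---|
| 0 | – | 40% v 15% | 0.852 / 0.798 |
| 10% | half | 38% v 14.25% | 0.826 / 0.766 |
| 20% | half | 36% v 13.5% | 0.799 / 0.731 |
| 30% | half | 34% v 12.75% | 0.770 / 0.692 |
| 30% | all | 28% v 10.5% | 0.664 / 0.560 |

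The last row is an extreme, since it needs every scan to be early.

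**5. Scenario tied to a figure in the article.** The Discussion cites 17% new lesions in the earlier Western study with atorvastatin given before CAS. If the assumed gain from 17% to 15% through longer dosing is not seen, 40% v 17% gives 0.775 / 0.709.

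**6. Unequal timing.** With no true effect, a 40% rate, L = 20%, half of one arm scanned early and none of the other, the false difference is 0.40 × 0.20 × 0.50 = 0.04. Rejection under the null rises from 0.050 to 0.074 (chi-squared) or from 0.030 to 0.047 (Fisher). This shows the mechanism and is not a prediction.

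**The case against.** - **The trial tests a whole perioperative regimen, not late emboli.** This stands. It limits the loss to the post-CAS part of the effect on silent lesions.
- **The power losses are assumed.** This also stands. The 40% control rate rests on lesions seen on DW-MRI in earlier studies, so it already reflects whatever scan times those studies used. Discounting it further supposes that this trial scans earlier, which the documents do not say.
- **Day 3 goes beyond the evidence on emboli.** The Discussion mentions only 1 day after CAS, which argues against day 0-1 scans but not against day 2. The reason for day 3 is different: it is when the randomised dosing ends.
- **Scan scheduling is detail for the full protocol.** This would hold if the article were silent. It states a rule, and the point concerns that rule.
- **Early discharge.** The Intervention section speaks of the remainder of hospitalization after the dosing period. That suggests, but does not establish, that patients are still in hospital on day 3, so a fallback is needed.

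Two stronger readings are tempting. A reader might infer that Outcomes contradicts the Abstract by giving imaging 30 days. The 30 days can equally attach to TIA or ischemic stroke alone, only one post-CAS scan is scheduled, and the secondary outcomes give imaging 5 days. The sentence is ambiguous, not contradictory. A reader might also infer that open treatment biases scan timing. Incomplete masking makes this possible, but nothing in the documents shows that scan day depends on arm.

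**Conclusion.** The point holds in a limited form. The scan window has no lower bound and spans the randomised post-CAS dosing, so the imaging component may be read before part of the effect that the article relies on for its 15% rate. With timing equal by arm, the result is dilution: chi-squared power between 0.826 and 0.770 instead of 0.852, or Fisher between 0.766 and 0.692 instead of 0.798. These figures assume 55 evaluable per arm, 10% to 30% late lesions and half of scans early. Bias would need unequal timing by arm, which is possible but not shown. No sample-size figure is wrong because of this point. The change is worth making because it is cheap and Fisher power has no reserve against a 0.80 target.

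**What to change.** 1. In the Intervention section, keep the single scan and the 5-day limit, but schedule it after the randomised dosing period, on day 3 to day 5 after CAS, by the same rule in both arms. If a patient leaves earlier, scan at discharge so that no result is lost.
2. Record the CAS-to-scan interval and compare it by arm.
3. Add a sensitivity analysis restricted to scans in the target window.
4. As a minor wording point, restate the primary outcome under Outcomes and in the Appendix table with the Abstract's separate windows: protocol DW-MRI within 5 days, TIA or ischemic stroke within 30 days. This also settles whether an unscheduled scan on days 6 to 30 counts.

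**Cost.** No extra scan and no change to treatment. There is less scheduling freedom, and some early-discharge scans will fall outside the target. The Appendix gives first enrolment as August 21, 2017 and the status as recruiting, so patients already scanned followed the wider window. Their scan dates should be retrieved so that they can be included in the comparison by arm and the sensitivity analysis.

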### MRI Protocol

MRI was performed using a 1.5T imaging unit (Optima MR360, G.E. Medical Systems). Sequences were applied at the same level, with the same slice thickness and same cut number. Slice thickness comprised the cut thickness (5 mm) plus gap (10 per cent). The standard number of slices was 20.

New ischemic lesions in the brain were defined as hyperintense lesions on postintervention diffusion-weighted imaging that were not present on pretreatment MRI. The pre- and post-operative DW-MRI findings will be compared. New ischemic lesions will be recorded based on the following criteria: whether any are present, their localization, their total number, their maximum diameter (with fully separated lesions on the same level or continuous levels being considered to be a single lesion; Ischemic foci localization will be recorded as “ipsilateral,” “contralateral,” or in “posterior circulation” relative to CAS). Two neuroradiologists with more than 10 years of experience, blinded to patient history and intervention procedure information, will independently analyze all MRI images and will discuss and agree upon these results when their judgements are inconsistent. If no consensus could be reached, a third reviewer had the final decision.

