## Appendix

**Table T1:** **Trial registration data set**.

**Data category**	**Information**
Primary registry and trial identifying number	ClinicalTrials.gov NCT03079115
Date of registration in primary registry	March 14, 2017
Secondary identifying numbers	121-2016006
Source (s) of monetary or material support	Beijing Hospital
Primary sponsor	Beijing Hospital
Secondary sponsor (s)	
Contact for public queries	[name] [contact]
Contact for scientific queries	[name]. [contact]
Public title	Efficacy of Two Different Doses of Atorvastatin for Prevention of Periprocedural Ischemic Brain Damage in Chinese Patients Undergoing Carotid Artery Stenting (CAS)
Scientific title	Effects of High dose of atorvastatin for Preventing periprocedural Ischemic brain damage in patients undergoing Carotid Artery Stenting (PICAS) in China: A Randomized Controlled Clinical Trial
Countries of recruitment	CHINA
Health condition (s) or problem(s) studied	Carotid Stenosis, Carotid artery stenting, High-dose statin therapy
Intervention (s)	High-dose Atorvastatin Arm: (80 mg/day from 3 days before to 3 days after CAS, and thereafter 20mg/day until 30 days after CAS) Conventional-dose Atorvastatin Arm: (20 mg/day from 3 days before to 30 days after CAS).
Key inclusion and exclusion criteria	Ages Eligible for Study: 40 Years to 90 Years (Adult, Older Adult) Sexes Eligible for the study: both Inclusion criteria: ≥ 50% stenosis of the internal carotid artery in symptomatic patients; or ≥ 70% stenosis of the internal carotid artery in asymptomatic patients received statin therapy for ≥ 2weeks before inclusion Exclusion criteria: nonatherosclerotic carotid disease (dissection, radiation-induced stenosis) received endovascular procedure within 30 days before inclusion CAS during the procedure of urgent endovascular therapy for acute ischemic stroke
Study type	Interventional (Clinical Trial) Allocation: randomized Intervention model: parallel assignment Masking: single(outcomes assessor) Primary purpose: treatment
Date of the first enrolment	August 21, 2017
Target sample size	130 participants
Recruitment status	Recruiting
Primary outcome (s)	Cumulative incidence of new ischemic lesion on post-CAS cerebral DW-MRI, TIA or ischemic stroke within 30 days after CAS
Key secondary outcomes	incidence of new ischemic lesion on post-CAS DW-MRI; number of new lesions on post-CAS DW-MRI; incidence of new lesion > 5 mm on post-CAS DW-MRI

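### As printed, the DW-MRI counting rule merges separate lesions, so it undercounts the secondary outcome of lesion number

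*Protocol article*

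**What the plan says.** The MRI Protocol section defines a new lesion as hyperintensity on the post-procedure diffusion images that was absent before treatment. The readers then record "whether any are present, their localization, their total number, their maximum diameter", and a parenthesis directly after that list gives the counting rule: "with fully separated lesions on the same level or continuous levels being considered to be a single lesion". The same parenthesis says that foci are coded as ipsilateral, contralateral or posterior circulation. Two neuroradiologists, blinded to patient history and procedure information, read independently. They settle disagreements by discussion, and a third reviewer decides if that fails.

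The acquisition details are "Slice thickness comprised the cut thickness (5 mm) plus gap (10 per cent") and "The standard number of slices was 20".

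Two measures rest on this reading. In the Outcomes section, secondary outcome 2 is "the number of new lesions and the incidence of new lesions >5 mm in size as detected via DW-MRI within this 5-day postoperative period". The registration data set in the Appendix lists "number of new lesions on post-CAS DW-MRI; incidence of new lesion > 5 mm on post-CAS DW-MRI" among the key secondary outcomes. No other section gives a different counting rule or says how the diameter of a merged lesion is measured.

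**The concern.** A lesion count normally merges signal that is connected and counts apart what is separate. The printed sentence merges lesions that it itself describes as fully separated, and it says nothing about connected signal, which is the case that needs a merging rule. Followed as written, any number of distinct foci on one slice, or in an unbroken run of slices, scores 1.

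The loss grows with lesion burden, so if one arm has more lesions per affected patient, its count is cut more and the contrast shrinks. The maximum diameter sits in the same list as the count, so the size outcome could be touched as well.

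**Working it through.** The plan has no figure for lesion number to reproduce. Its sample size concerns the binary primary endpoint and does not depend on the counting rule.

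**Which outcomes can change.** Merging turns a count of 2 or more into a smaller count that is still at least 1. It never turns a positive scan negative. The composite primary outcome and secondary outcome 1 (any new DW-MRI lesion) are therefore unchanged, and so is the sample size. The number of lesions can change.

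**Size of the undercount.** The documents give no lesion-count data, so this is an illustration. Assume that k separate lesions each fall independently and uniformly on S slices, and that lesions on the same or adjacent slices are merged. The recorded count is then the number of runs of occupied slices. A run starts at slice 1 if slice 1 is occupied, or at any later slice that is occupied while the one before it is empty. With a = ((S−1)/S)^k and b = ((S−2)/S)^k, the expected recorded count is

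E = (1 − a) + (S − 1)(a − b).

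S = 20 is the protocol's slice number. S = 12 is an assumption that the lesions lie in part of the brain.

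- S = 20, k = 3: a = 0.8574, b = 0.7290; E = 0.1426 + 19 × 0.1284 = 2.58
- S = 20, k = 5: a = 0.7738, b = 0.5905; E = 0.2262 + 19 × 0.1833 = 3.71
- S = 12, k = 3: a = 0.7703, b = 0.5787; E = 0.2297 + 11 × 0.1916 = 2.34
- S = 12, k = 5: a = 0.6472, b = 0.4019; E = 0.3528 + 11 × 0.2454 = 3.05

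| True lesions | Recorded, S = 20 | Recorded, S = 12 |
|---|---|---|
| 1 | 1.00 | 1.00 |
| 3 | 2.58 | 2.34 |
| 5 | 3.71 | 3.05 |
| 10 | 5.15 | 3.41 |

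The true ratio 5/3 = 1.67 becomes 3.709/2.582 = 1.44 on 20 slices and 3.052/2.337 = 1.31 on 12.

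The recorded count need not even rise with burden: at S = 12, 20 true lesions give an expected count of about 2.5, below the 3.05 for 5 lesions. On 20 slices it cannot exceed 10.

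**Effect on a between-arm test.** The table is conditional on patients who have lesions. For the whole-arm comparison I simulated a U-test, one of the tests named under Statistical Analyses, at two-sided 0.05 with 56 patients per arm. I used 1,500 runs per case and assumed geometric counts among lesion-positive patients.

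| Lesion presence | Mean count if positive | Slices | Power, true counts | Power, merged counts |
|---|---|---|---|---|
| 40% vs 15% | 5 vs 3 | 12 | 0.88 | 0.87 |
| 40% vs 15% | 5 vs 3 | 20 | 0.90 | 0.89 |
| 40% vs 25% | 5 vs 3 | 12 | 0.50 | 0.47 |
| 40% vs 25% | 5 vs 3 | 20 | 0.53 | 0.52 |

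Repeat simulations of these cases differ by about 0.01 to 0.02 from Monte Carlo error. The rank test loses little because most patients score 0 in both arms and merging cannot alter a 0.

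**Size outcome.** Taking the gap as 10% of the cut, slice spacing is 5 × 1.10 = 5.5 mm. Two foci of 5 mm or less, on adjacent slices or apart on one slice, could span more than 5 mm if diameter is taken across the merged group. If only the largest component is measured, the per-patient incidence of a lesion over 5 mm does not change. The text does not say which applies.

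**The case against.** The strongest reply is that the sentence is awkward English for the ordinary rule, that each fully separated lesion counts as one. The side coding in the same parenthesis supports this: under the literal rule, an ipsilateral and a contralateral focus on one slice would become one lesion with no side to assign. The readers are experienced neuroradiologists, and nothing shows that they scored scans as printed. The article also condenses a fuller protocol. This stands as a reason not to assume that the data are damaged. It does not rescue the sentence, which states a rule rather than leaving one out and is corrected nowhere else.

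Three stronger readings are tempting, and the documents support none of them.

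- A reader might infer that the outcome for lesions over 5 mm is also corrupted. That needs diameter to be measured across a merged group, which the text does not say.
- A reader might infer that any difference between the arms shrinks. Patients with 0 or 1 lesion are untouched, and in the simulated U-test cases the power loss was at most a few points. A t-test or a reported mean count would be affected more.
- A reader might infer that the main result is at risk or that the rule favours one arm. The binary endpoints do not change, and blinded readers apply the same rule to both arms.

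**Conclusion.** The counting sentence is wrong as printed. Under its literal meaning, the number of new lesions is too low in any patient with two or more separate foci on the same or consecutive slices. That direction needs no assumption about where lesions fall. The amount does: the fall in the ratio from 1.67 to about 1.44 or 1.3 rests on random placement, on 20 or 12 involved slices, and on 5 against 3 lesions in lesion-positive patients.

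One part of one secondary outcome is affected for certain under the literal rule, and the other part, size, only conditionally. Whether any recorded data are affected depends on the rule that the readers actually used, which the article does not show. Severity is moderate.

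**What to change.** Rewrite the sentence along these lines: hyperintensity that is connected within a slice, or continuous across adjacent slices, counts as one lesion; each fully separated hyperintensity counts as its own lesion; maximum diameter is measured per connected lesion. Give this wording to the readers before further scans are scored.

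Ask the readers which rule they have applied so far, and record the answer. If they already counted separate foci separately, only the text changes. If they followed the printed wording, the existing blinded readers should re-score the stored scans for number and diameter.

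The cost is one sentence and one query to the readers, plus a re-read only in the second case. The Appendix lists the trial as recruiting, so early correction limits how many scans a re-read would involve. The sample size, the primary outcome and the any-new-lesion outcome need no change.
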